#### Sample size and power

Schools are the units of cluster-randomization. A conservative power estimation with an expected effect size of 0.42 for the main outcome (general math, based on results from [17]) and an intra class correlation of 0.15, resulted in a sample of ≥ 9 schools per intervention arm (27 in total), with a mean of 20 children per class and a minimum of one class per school (power 0.8, 1-tailed, α = 0.05). Mixed-effects models will be used to test the between-group difference (intervention vs. control) for the main outcome (general Math), controlling for baseline values and including school and class as random effects [41].

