### Randomized controlled trial (RCT)

The overall aim of the ACTIVE SCHOOL RCT study is to investigate the effects of two different types of in-school PA interventions on academic performance in children aged 9–10 years (3rd grade). The cluster RCT has three arms and includes two intervention groups; (1) RJF and (2) ML, and (3) control group (CG). The interventions are planned for one school year carried out in two rounds during the school years 2023/2024 and 2024/2025. The randomization will be stratified at the school level with an approximate 1:1:1 recruitment protocol (RJF:ML:CG). Approximately nine schools will be allocated to each arm (see *Randomization*). Due to the study design, blinding of instructors, teachers and participants will not be possible, which is common practice in school-based studies.

Schools from all regions of Denmark will be recruited by phone, e-mail, relevant websites, and digital/social media targeting school staff and school principals. If principals and school staff agree to participate in the study, an informal project meeting will be held, and comprehensive information will be provided.

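### The stated power of 0.80 with nine schools per arm does not follow from the stated inputs, which give about 0.65 for each intervention-control comparison

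*Protocol article*

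**What the plan says.** The section on sample size and power of the protocol article gives a full set of inputs and a result. The inputs are an "expected effect size of 0.42 for the main outcome" (general math), "an intra class correlation of 0.15", a mean of 20 children per class with at least one class per school, and "power 0.8, 1-tailed" with alpha 0.05. The result is at least nine "schools per intervention arm (27 in total), with a mean of 20 children per class and a minimum of one class per school". The calculation is described as conservative.

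The same section says "Schools are the units of cluster-randomization". It then names the test as intervention versus control on general math, in a mixed model that controls for baseline values and has school and class as random effects. The section on the randomised controlled trial describes three arms and repeats the allocation: "Approximately nine schools will be allocated to each arm". The randomization section confirms 27 schools.

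The article gives no baseline-outcome correlation or variance reduction for the calculation. It does not say whether the ICC refers to school or class, and it does not define power in any way other than for an intervention-control comparison.

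**The concern.** The inputs needed to check the figure are printed beside it, and the usual cluster-randomised calculation does not return that figure. A detail left to a fuller document would be no finding, but this is a numerical result that is said to come from the listed inputs. It is also the article's justification of the sample size for the primary outcome. A reader who meets a null result on math will judge it by the stated power and effect size. If the calculation rested on an assumption that is not shown, the reader needs that assumption in order to judge it.

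**Working it through.** **Inputs** (all from the section on sample size and power): d = 0.42 in SD units; ICC = 0.15; m = 20 children per school (one class per school, the stated minimum); k = 9 schools per arm; one-tailed alpha 0.05 (z = 1.645); power 0.80 (z = 0.842). With one class per school, class and school are the same cluster, so the level of the ICC makes no difference to the base case.

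**Design effect:** 1 + (m − 1) × ICC = 1 + 19 × 0.15 = 3.85.

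**Schools required for 0.80**
- Children per arm without clustering: 2 × ((1.645 + 0.842)/0.42)² = 70.1.
- With clustering: 70.1 × 3.85 = 269.9 children per arm.
- Schools: 269.9/20 = 13.49 per arm, against the stated 9.

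**Power at 9 versus 9 schools**
- SE of the difference: √(2 × 3.85/180) = 0.2068.
- Standardised difference: 0.42/0.2068 = 2.031.
- Normal approximation: Φ(2.031 − 1.645) = 0.65.
- Noncentral t with 16 df (18 schools − 2): 0.62.

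**Detectable effect at 9 per arm, power 0.80:** (1.645 + 0.842) × 0.2068 = 0.51 SD.

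The stated 0.80 is therefore not reproduced. Two other readings keep the stated inputs (one-tailed, normal approximation):

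| Reading | Calculation | Power |
|---|---|---|
| Both interventions pooled against control, 18 v 9 schools | SE = √(3.85/20 × (1/9 + 1/18)) = 0.179 | 0.76 |
| Two classes per school (m = 40), ICC at school level | design effect 6.85; SE = √(2 × 6.85/360) = 0.195 | 0.69 |
| Upper limit of the second reading: unlimited children per school | SE = √(2 × 0.15/9) = 0.183 | 0.74 |

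Power of 0.80 is reached only by adding or changing an input. These routes were found:

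| Input that the article does not state | Power |
|---|---|
| Baseline-outcome correlation r = 0.5, variance multiplied by (1 − r²) | 0.76 (0.73 with 16 df) |
| r = 0.577 | 0.80 (0.77 with 16 df) |
| r = 0.6 | 0.81 (0.78 with 16 df) |
| r = 0.7 | 0.88 (0.86 with 16 df) |
| School-level ICC of 0.08 instead of 0.15 | 0.81 |
| Two classes per school, clustering at class level only (18 classes per arm) | 0.89 |
| Power defined as winning at least one of two unadjusted one-tailed tests, both true effects 0.42, correlation 0.5 through the shared control arm | 0.80 |

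The rows for r assume that the baseline score removes the same share of variance between schools as within them.

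**Possible origin of 27:** 2 × 13.49 = 26.99, so 27 is close to the total for a two-arm trial. The match is not exact in whole schools: 13 v 14 schools gives 0.7997, and two equal arms need 28.

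**The case against.** The strongest defence is that the sentence after the power figure commits the analysis to baseline adjustment, and a correlation of about 0.58 restores 0.80 under the normal approximation. This stands as a limit on the conclusion. A reader might infer that the trial is underpowered, or that it has about a one-in-three chance of missing a true 0.42 SD effect (1 − 0.65 = 0.35). The document does not support that, because 0.65 describes an unadjusted comparison. The defence does not rescue the printed figure. No correlation is among the listed inputs, and the section on the math test specifies different tests at the two time points (MAT2 before, MAT3 after), so the correlation has to be declared.

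A second defence is that 20 is the mean class size and one class is the minimum, while the level of the ICC is left open. If a school has two classes and clustering exists only between classes, power is 0.89. That reading sets school-level clustering to zero, although schools are randomised and the model has a school effect. With the ICC at school level, extra classes take power no higher than 0.74.

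A reader might also infer that a two-arm total of 27 was spread over three arms. The arithmetic allows this, but the document does not say how 27 arose, and power to win at least one comparison also comes to about 0.80. It remains an inference.

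Finally, the lack of a stated allowance for non-consent or dropout is not counted here, since a condensed article may leave that to the full protocol.

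**Conclusion.** The point holds as an error in the stated power. On the printed inputs, with one class of 20 per school and the ICC at the level of the randomised school, each intervention-control comparison has power of about 0.65 (0.62 with 16 df), some 15 points below the stated 0.80. The same inputs need about 13.5 schools per arm, and nine per arm detect about 0.51 SD. Pooling the interventions or adding a second class under a school-level ICC does not close the gap.

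The conclusion rests on the standard design-effect calculation with equal cluster sizes and no covariate. It says that the figure does not follow from the inputs given. The power of the baseline-adjusted analysis may be 0.80 or more, depending on a correlation that the article does not give.

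**What to change.** Rewrite the power statement in one of two ways.

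1. Keep the inputs as printed and report power of about 0.65 (0.62 with 16 df) per intervention-control comparison, with a detectable effect of about 0.51 SD at 80% power.
2. If baseline adjustment was relied on, declare the assumed MAT2-MAT3 correlation with its basis, say whether the ICC of 0.15 is at school or class level, and give power over a range such as r = 0.5, 0.6 and 0.7. On the assumptions above that is 0.76, 0.81 and 0.88 (0.73, 0.78 and 0.86 with 16 df). If a different ICC or definition of power was used, state that instead.

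In either case, drop the word conservative unless the restated calculation supports it. The cost is rewording one paragraph. Schools, allocation, data collection and the analysis model stay as they are, and no extra schools are needed. The stated power becomes less favourable unless the missing input is declared and justified.

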## Abstract

**Background:**

Previous research has suggested that school-based physical activity (PA) interventions may have a positive impact on academic performance. However, existing literature on school-based interventions encompasses various forms of PA, spanning from vigorous intensity PA outside the academic classes to light intensity PA and movement integrated into academic learning tasks, and results on academic performance are inconclusive. ACTIVE SCHOOL will implement two different PA interventions for one school year and assess the effects on the pupils’ academic performance, with math performance as the primary outcome.

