#### Plan for data management, analysis, and statistics

Descriptive statistics across groups will be summarized and presented. Flow diagram of participants will be described and presented according to the Consolidated Standards of Reporting Trials (CONSORT) 2010 for randomized controlled trials [64]. Differences at baseline between participants included and excluded in the main analyses will be presented (e.g., drop-out analyses) and data will be analyzed for between-group differences (interventions vs. control) at baseline for all outcomes. The effects of the intervention on both primary and secondary outcomes will be tested in intention-to-treat analysis using multilevel mixed models with group (interventions/control) as fixed effect and adjusted for relevant confounders not evenly distributed between groups at baseline. School and class will be included as random effects in the model to account for the cluster structure of the data. Furthermore, per-protocol analysis will be performed including only children from classes compliant with the intervention principles (based on SMS-survey answers from teachers/pedagogues). The statistical analysis will be performed using R (R Core Team, 2022) and in the IMB Statistical Package for the Social Sciences (SPSS) version 24.

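### The power calculation for math rests on an unjustified one-tailed 5% level, the only error rate stated; at two-sided 5% the stated 80% power does not apply

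*Protocol article*

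**What the plan says.** The section on sample size and power gives the design level as "power 0.8, 1-tailed", with an alpha of 0.05. The other inputs are an "expected effect size of 0.42 for the main outcome", an "intra class correlation of 0.15", and nine schools per arm (27 in total) "with a mean of 20 children per class and a minimum of one class per school". The article calls this estimation conservative.

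The next sentence of that section describes a mixed model comparing intervention with control on general math, adjusted for baseline, with school and class as random effects. It gives no sidedness. The section on data management, analysis and statistics also gives neither sidedness nor a significance level.

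The section on the randomized controlled trial sets up three arms at about 1:1:1: Run, Jump & Fun (RJF), Move & Learn (ML) and one control group (CG). The outcome measures section names both interventions as the subject of the effect assessment, with math as the primary outcome. The discussion says that the effects of both approaches will be tested. On prior evidence, the abstract states that "results on academic performance are inconclusive".

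**The concern.** A one-tailed 5% test accepts the same strength of evidence for benefit as a two-sided 10% test. That is the lenient choice, so it sits badly with the label conservative, and no reason for it is given. The prior evidence is described as unsettled. Both programmes take 4 × 30 minutes a week of the school day, in ML's case inside math and Danish lessons, so a negative effect on math would be a result worth being able to report.

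The choice has consequences either way. If the analysis uses the printed level, the standard for a positive primary result is looser than readers will assume from the word significant, and two interventions each get a chance at it. If the analysis uses two-sided 5%, the advertised power belongs to a different test. Leaving the matter open until results are seen would let sidedness decide whether the primary result counts as positive.

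**Working it through.** **Inputs (Sample size and power section).** Effect size d = 0.42; intraclass correlation 0.15; m = 20 children per school (one class); k = 9 schools per arm; alpha 0.05 one-tailed; target power 0.80. Equal arms with a shared control come from the section on the randomized controlled trial.

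**1. The plan's own figure.**
- Unclustered n per arm = 2 × [(1.645 + 0.842)/0.42]² = 70.1.
- Design effect = 1 + (20 − 1) × 0.15 = 3.85.
- Schools per arm = 70.1 × 3.85/20 = 13.5, so 14.

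The printed nine schools do not follow from the printed inputs alone. Nine schools give an effective n of 180/3.85 = 46.75 per arm, a standard error of √(2/46.75) = 0.207, and 0.42/0.207 = 2.03. One-tailed power is Φ(2.03 − 1.645) = 0.65. Nine schools reach 0.80 one-tailed only with an unstated gain, for example a baseline covariate explaining about 33% of the variance (r about 0.58). This is a separate matter. It is why the cost of a two-sided test is shown below on several bases.

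**2. False claims of benefit if the printed level is used for both contrasts.** RJF−CG and ML−CG share a control and the arms are equal, so the two test statistics correlate 0.5. With both null hypotheses true:
- One-tailed 5% each: 1 − P(Z₁ < 1.645, Z₂ < 1.645) = 0.088 (0.087 by simulation with t on 24 df).
- Two-sided 5% each, benefit direction: 1 − P(Z₁ < 1.960, Z₂ < 1.960) = 0.045. Counting false claims in either direction, the rate is 0.091.

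The like-for-like effect of sidedness on false claims of benefit is therefore 8.8% against 4.5%.

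**3. Power at nine schools per arm, one-tailed against two-sided 5%.**

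*(a) If nine schools truly give 80% one-tailed:* two-sided power = Φ(1.645 + 0.842 − 1.960) = Φ(0.526) = 0.70. Restoring 80% would take 9 × [(1.960 + 0.842)/(1.645 + 0.842)]² = 11.4, so 12 schools per arm.

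*(b) Printed inputs, no covariate gain:* Φ(2.03 − 1.960) = 0.53, down from 0.65.

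*(c) With baseline adjustment.* The article plans this adjustment but gives no correlation r, so r is an assumption here. The variance is multiplied by 1 − r², at school and child level alike.

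| r | 0.42/SE | One-tailed 5%, normal | Two-sided 5%, normal | Two-sided 5%, t (16 df) |
|---|---|---|---|---|
| 0 | 2.03 | 0.65 | 0.53 | 0.48 |
| 0.5 | 2.35 | 0.76 | 0.65 | 0.60 |
| 0.7 | 2.84 | 0.89 | 0.81 | 0.76 |
| 0.8 | 3.38 | 0.96 | 0.92 | 0.89 |

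The cost of moving to two-sided 5% is read along a row, because comparing rows changes the covariate assumption as well. By normal approximation it is about 12 points at r = 0, 11 at 0.5, 7 at 0.7 and 4 at 0.8.

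**The case against.** The strongest reply is that the one-tailed level appears once, among the inputs of the power estimation. No sentence describing the analysis fixes the final test as one-sided, and a mixed model gives an estimate and an interval in both directions. This stands. A reader might infer that harm cannot be tested in this trial, or that the false-benefit rate is 9% as a fact about the plan. The article supports neither without condition: both require the final test to follow the design level, and the 9% also requires two separate unadjusted contrasts, which the article does not spell out.

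A reader might also infer that the lack of a multiplicity rule is itself an error. It is not shown to be one. A condensed article may leave this to the statistical analysis plan, and whether two distinct interventions against one control need adjustment is debated.

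A third reply is that the background section reports reviews finding mostly a positive relation or none, which is some basis for expecting a direction. That explains an expectation of benefit. It does not justify halving the evidence required, and the article does not offer it as a justification.

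Finally, baseline adjustment is already planned and may bring two-sided power near or above 80%. That is true if the correlation is about 0.7 or higher by normal approximation, but the article states no correlation.

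**Conclusion.** The concern holds in a conditional form. The one error rate that the article states is a one-tailed 5% level, without justification and described as conservative. Under either reading of the final test something has to change:

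- If the test follows the printed level for both contrasts, the chance of at least one false claim of benefit is about 8.8%, and a negative effect on math could not be declared significant.
- If the test is two-sided 5%, the stated 80% power does not describe it. Power is about 0.70 if 80% one-tailed is taken as given, 0.53 from the printed inputs alone, and about 0.65 to 0.92 (normal) or 0.60 to 0.89 (t, 16 df) if the baseline correlation is 0.5 to 0.8.

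The 8.8% assumes equal arms, a shared control and no adjustment. The power figures assume one class of 20 per school, and the last range rests on an assumed correlation.

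**What to change.** State that the primary outcome is tested two-sided at 5% and reported with 95% confidence intervals. Restate the power for nine schools per arm on that basis, with the assumed correlation between baseline and final math score shown. Do both before any outcome data are seen by arm.

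The cost is a change of wording and a less favourable stated power. Recruitment and the interventions need not change. The planned baseline adjustment limits the loss, but it is already part of the design and should not be counted as a new gain.

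As an option, name RJF−CG and ML−CG as the primary contrasts and say whether they are handled with Holm or Dunnett or left unadjusted with a reason. If Bonferroni is taken as a simple bound for the cost of adjustment (two-sided 2.5% each), power falls from 0.70 to about 0.60 under basis (a). The analysis plan may already cover this.

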#### Outcome measures

To evaluate the effects of the interventions, children will be assessed before (T0) and after the intervention period (T1). Assessments will be carried out by research staff trained by senior research team members of ACTIVE SCHOOL and will be performed during school hours. Outcomes measured to assess potential effects of the two interventions (RJF and ML) include academic performance in math (primary outcome) and Danish, cognitive functions (working memory tasks), motivation for school, well-being, anthropometry, cardiorespiratory fitness, and physical activity level as secondary outcomes. Data entry will be performed onsite in REDCap using laptop computers and written on paper for random sample quality testing. REDCap is a secure web application for building and managing online surveys and databases [42]. Additionally, objective PA measures will be conducted at T0, T1 and at some schools also during the intervention. Implementation outcomes will be assessed on a regular basis (see below).

#### Academic performance tests

Standardized academic tests in Danish and math will be performed by school’s teachers, who will follow the test team’s written and oral instruction given in advance. The academic tests will be conducted early on the school day, before any school-based PA is initiated to avoid acute effects. The tests will be performed on computers in the classroom before the intervention start (T0) and in the end of the intervention period (T1). The children will be placed at distance to avoid copying.

Test results will be collected and administered by Hogrefe, a publisher of psychometric assessments and psychology books and journals. Data from tests will be securely transferred to ACTIVE SCHOOL research team and stored on a secure drive. The tests from Hogrefe are commonly used in educational practice in Denmark [43–46].

##### Standardized Test in Math

A standard, diagnostic, computerized test will be used to evaluate children’s math proficiency in relation to second (MAT2 assessed at T0) and third-grade (MAT3 at T1) proficiency [45]. Fifty problems from arithmetic (addition, subtraction, and multiplication), geometry, and probability will be included in the test. Children will be positioned in front of a computer, given the task of solving all 50 problems to the best of their abilities. The test is conducted during one school-week at several timeslots and managed to the manufactory description. The quantity of problems that are successfully solved will be the outcome indicator.

##### Standardized Reading Tests in Danish

Standardized Reading Comprehension Test: A valid and reliable Danish reading comprehension test (Sætningslæseprøve 2) will be used to evaluate the children’s reading abilities [44]. The test will be performed online and instructed by the Danish teacher. The test is appropriate for children in 3rd grade, and will be used both at baseline (T0) and at the end of the intervention (T1). The test includes 27 drawings of situations that are each accompanied by four statements. The child must check a true or false box next to each statement to indicate whether the text agree with the situation depicted in the drawing. The complexity and length of the sentences will increase gradually. Following the test protocol, eight minutes will be allotted for the child to complete as many statements as they can. The number of statements correctly evaluated will serve as the outcome.

##### Standardized Word Reading Test

The word reading test (Ordlæseprøven 2) assesses children’s word reading ability and will be administrated strictly according to the manufacturer’s description [46]. Within four minutes, children must read as many words as possible. The test is a multiple choice with four drawings for each printed word. Each child should read the word and choose the matching drawing. The test outcome is the number of correctly read words in four minutes.

#### Anthropometric and demographic variables

Participants’ height will be measured using a stadiometer (West Sussex, UK) with a precision of 0.5 cm. Body weight will be measured to one decimal (0.1 kg) using an electronic scale (Tanita WB-150 SMA, Tokyo, Japan) and the children will not be able to see their weight measure. Overweight and obesity will be determined based on age- and gender-specific body mass index (BMI) reference values [47]. Waist circumference will be measured to the nearest 0.5 cm above the navel, with a minimum of two measurements taken. If the measurements differ by more than 2.0 cm, a third measurement will be performed and the average of the two closest measurements will be used. Participants will self-report their puberty stage using a questionnaire, which consists of five categories of secondary sex characteristics defined by Tanner [48], using standardized color images as suggested by Carel and Leger [49]. Information on pubic hairs development in boys, and menstruation (yes/no), breast and pubic hair development in girls will be collected.

